**Methods:**

This is a single-blind randomized controlled trial. Randomization will be done through simple random sampling. The population and sample of the study include all patients with deep neck abscesses treated at [name] Hospital, which is equipped with board-certified otorhinolaryngologists. Patients with deep neck abscesses who were given ethical clearance and meet the inclusion criteria were recruited as study participants until the sample size was reached. There are 18 participants in each group. Participants in the intervention group received standard dressings in addition to honey dressings, whereas those in the control group received standard dressings alone. Proinflammatory cytokines and growth factors, wound size, Bates-Jensen Wound Assessment Tools scoring, and quantitative bacterial colony identification will be all evaluated and assessed. The gathered data will be documented and subjected to statistical analysis.

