Wound size (length, width, and depth): Wound size was measured by a trained research assistant. The measurement was conducted with a specific ruler and probe. The width and length recorded were the largest calculated amounts, whereas the depth of the wound was measured using a specific probe inserted perpendicularly to the meeting point of the length and width until it reached the base of the wound. To enhance measurement precision and reproducibility, the ImitoMeasure wound documentation app was also used [36]. This mobile app enables photographic documentation with calibrated scale indicators, providing consistent digital measurements of wound area and depth. This measurement was conducted by the research assistant 3 times, and the results were averaged to obtain a more accurate wound size estimate.BWAT: The raw wound data and clinical wound appearance were first recorded by an assistant. The final scoring and interpretation based on these observations were conducted independently by the principal investigator, who was blinded to treatment allocation during the evaluation process.Wound swabs for bacterial culture: Infection was considered to have improved as evidenced by bacterial culture findings and the number of bacterial colonies that proliferated. Samples were collected by the clinical team under sterile conditions and submitted to a certified microbiology laboratory for quantitative colony count analysis. Samples were taken from the wound base using sterile cotton, placed in Amies transport medium, and delivered to a microbiological laboratory.Tissue biopsy for cytokine (IL-1 and TNF-α) and growth factor (VEGF) analysis: Tissue biopsy was performed by an otorhinolaryngology resident using standard sterile technique. The biopsy samples were then processed by trained laboratory personnel for immunohistochemical examination.

On day 7, wound size measurements and BWAT scoring were repeated using the same tools and by the same assessors as on day 1 to ensure consistency across time points.

On day 14, all baseline measurements were repeated, including wound size, BWAT scoring, wound swab cultures, and tissue biopsies for cytokine and growth factor quantification. The same assigned personnel performed all assessments to reduce interobserver variability and enhance the reliability of longitudinal comparisons. The schedule of interventions and sample measurements is illustrated in Figure 1.

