### Outcomes

In this study, a research assistant collected samples after completing wound dressing and storing the dressing materials. Measurements were taken on the first, seventh, and fourteenth days for BWAT assessments, as well as the first and fourteenth days for bacterial colony identification from wound bed swabs and cytokine and growth factor expression analysis from tissue samples. The resident doctor was accountable for the dressing and performed pus aspiration and tissue sampling. All information was meticulously documented on an authorized form. Wound measures included length, width, and depth, with data based on the largest width and length. Wound depth was measured using a probe perpendicular to the wound’s length and width. BWATs were evaluated by an uninformed research assistant. Bacterial culture findings and the number of bacterial colonies were used as evidence of infection improvement. Swabs from the wound bed were delivered to the microbiology lab. Tissue samples were sent to the Anatomical Pathology lab for immunopathological examination of wound healing, including quantification of IL-1, TNF-α, and VEGF expression. Tissue samples were collected using nasopharyngeal biopsy forceps, and the preserved tissue was sent out for analysis. Additionally, laboratory examinations, radiographs, and patient comorbid factors were documented for analysis in the case report form.

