### Statistical Analyses

The Shapiro-Wilk test will be used to assess the normality of continuous data because the sample size is less than 50. For comparison of wound healing outcomes between the honey dressing and standard dressing groups at each time point (days 1, 7, and 14), either an independent *t* test or Mann-Whitney U test will be used, depending on data distribution. To analyze the overall effect of treatment over time and assess the interaction between treatment group and time, a generalized estimating equation analysis will be performed. A *P* value of <.05 will be considered statistically significant. All data will be analyzed using SPSS software version 25.0 (IBM Corporation) and presented in tables summarizing the changes on days 1, 7, and 14 (Figure 2).

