## Results

This manuscript presents a study protocol for a randomized controlled trial investigating honey as a wound care modality in patients with DNSAs. Ethical approval and partial funding for the study were obtained in May 2024. Recruitment and data collection commenced in June 2024 and was completed in May 2025. As of manuscript submission, the full sample of 36 participants has been successfully enrolled (Figure 3). Data analysis is currently underway, and the study results are expected to be submitted for publication in early 2026.

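### The GEE group-by-time test rests on 36 participants with no small-sample correction stated; with the usual uncorrected robust Wald test, nominal 5% becomes about 8% (three visits) or 6.5% (two visits)

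*Protocol article*

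**What the plan says.** The Statistical Analyses section gives two layers of analysis. At each visit the groups are compared by a t test or a Mann-Whitney test. Across visits, for the treatment effect over time and the group-by-time interaction, "a generalized estimating equation analysis will be performed". The threshold is the same for everything: "A *P* value of <.05 will be considered statistically significant". The software is SPSS 25.0. The section gives no working correlation, covariance estimator, reference distribution or small-sample correction, and does not say whether time is categorical or linear.

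The number of independent units is small and already fixed. The Abstract says "There are 18 participants in each group", and the Results section says that "the full sample of 36 participants has been successfully enrolled".

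The outcomes differ in their number of visits. Wound size and BWAT are taken on days 1, 7 and 14 (Measurements: "On day 7, wound size measurements and BWAT scoring were repeated using the same tools"). The laboratory outcomes have two visits only (Outcomes: "the first and fourteenth days for bacterial colony identification from wound bed swabs and cytokine and growth factor expression analysis from tissue samples").

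**The concern.** The robust (sandwich) variance used with GEE is estimated from between-participant variation in residuals, and its justification is asymptotic in the number of participants. With 18 per group two things go wrong, both in the same direction. The residuals are too small because the group means were fitted to the same data. The Wald statistic is then compared with a chi-square, as if the variance were known. P values come out too small and confidence intervals too narrow.

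The same section chooses its normality test because the sample is below 50, so the small sample was noticed there but not carried through to the longitudinal test. At stake is whether a group-by-time P value just under .05 can be taken at face value.

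**Working it through.** **Inputs.** From the article: 18 per group, three visits (wound size, BWAT) or two visits (colony counts, IL-1, TNF-α, VEGF), nominal 5%. Assumed, because the article is silent: uncorrected robust covariance, Wald chi-square reference, categorical time, complete data. The article gives no type I error figure to reproduce.

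**Step 1: size of the standard-error bias.** With group, categorical time and their interaction in the model and complete data, the GEE estimates are the group-by-visit means whatever the common working correlation. The uncorrected sandwich divides residual sums of squares by n rather than n − 1. The ratio of the standard error to its unbiased version is √(17/18) = 0.972, about 3% too small.

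**Step 2: three visits (2 df), normal data.** With equal groups, the uncorrected Wald statistic W equals (18/17) × Hotelling's T². With m = 36 − 2 = 34, T² × 33/(2 × 34) follows F(2, 33).
- Chi-square critical value (2 df): 5.991.
- Equivalent F value: 5.991 × (17/18) × 33/68 = 2.746.
- For numerator df 2 the tail area is (1 + 2x/33)^(−33/2). At x = 2.746 this is 1.1664^(−16.5) = 0.079.
- Removing only the standard-error bias: x = 5.991 × 33/68 = 2.907, tail area 0.069.
- Replacing the chi-square by the F reference as well: 0.050 by construction.

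Of the excess of about 2.9 points, about 1.0 comes from the standard error and about 1.9 from the reference distribution.

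**Step 3: two visits (1 df), normal data.** The test becomes |t| on 34 df against √(3.841 × 17/18) = 1.905, giving 0.065. Removing the standard-error bias alone gives 0.058.

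**Step 4: simulation over the unknowns** (100,000 null trials per setting, 18 per group; within-patient correlation 0 to 0.7, exchangeable or AR(1)):

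| Setting | Rejection rate |
|---|---|
| Three visits, robust, normal | 7.7–7.9% |
| Two visits, robust, normal | 6.4–6.6% |
| Linear time over three visits, robust, normal (correlation 0.5 only) | 6.3% |
| Three visits, robust, lognormal | 6.0–6.7% |
| Two visits, robust, lognormal | 5.4–5.8% |
| Three visits, model-based exchangeable, normal | 5.5–6.2% |
| Three visits, Kauermann-Carroll-type correction, chi-square, normal | 6.6–6.9% |
| Three visits, Mancl-DeRouen-type correction, chi-square, normal | 5.8–6.0% |
| Three visits, unbiased covariance, F reference, normal | 4.8–5.0% |

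The first two rows agree with Steps 2 and 3 and hardly depend on the correlation. A fitted exchangeable GEE (1,500 null trials, three visits, correlation 0.5) gave 8.5%, with a Monte Carlo standard error of about 0.7 points. With 200 per group, the uncorrected three-visit test falls to 5.3%, which confirms that this is a small-sample effect.

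The model-based row is limited to three visits and normal data. With lognormal data the same test gave 4.3–4.9%. With two visits its result depends on the divisor used when estimating the working correlation, so no figure is relied on here.

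**The case against.** The strongest reply is that the article never says robust standard errors or a chi-square will be used. It says only GEE, and a condensed article may leave the covariance and degrees of freedom to a full protocol or SAP that is not shown. This stands in part. It makes the error rates conditional, and if a suitable correction is specified elsewhere the problem disappears. It does not remove the point that a large-sample method was chosen for 36 participants.

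The second reply is that 8% is the top of the range. That is correct: most of the named outcomes have two visits, and colony counts may well be skewed.

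Three stronger readings are tempting, and the documents do not support them:
- **That the interaction is the trial's decisive test of honey.** No section says so. The Sample Size section is built on a single measurement compared between two groups, which matches the per-visit tests, and those are unaffected.
- **That GEE will be biased because losses depend on severity.** The Introduction gives departmental mortality, not dropout in this trial, and the participant flowchart is not available here. Severity-related loss is a possibility, not something the article shows.
- **That standard errors alone are to blame.** They are only about 3% too small. In the three-visit test the chi-square reference accounts for most of the excess.

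A final reply is that a linear mixed model brings a normality assumption of its own. That is fair, and it limits where the alternative applies.

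**Conclusion.** The concern holds in conditional form. If the planned GEE is run with an uncorrected robust covariance and a Wald chi-square, the true level at nominal 5% is about 8% for the three-visit interaction (wound size, BWAT) with categorical time and roughly normal data, and about 6.5% for the two-visit outcomes. Across the robust settings examined at 18 per group the range is 5.4–7.9%. The inflation is moderate. It matters mainly for results near the threshold, and it does not touch the t tests or Mann-Whitney tests at each visit. A reader might infer that the plan states an invalid test or that every interaction test rejects at 8%; neither follows from the article.

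**What to change.** Add one sentence to the analysis plan, choosing one of two routes:

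1. Keep GEE, with time as categorical, a small-sample-corrected covariance and a t or F reference. Correcting the covariance while keeping the chi-square is not enough for the three-visit test (5.8–6.9% remains).
2. For outcomes that are approximately normal, after transformation if needed, use a REML mixed model for repeated measures with unstructured covariance and small-sample degrees of freedom.

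Strongly skewed outcomes should be transformed under either route. On untransformed lognormal data the F-referenced test turned conservative (3.2–4.2%).

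The Results section says that analysis is under way, so this should be recorded as a dated change, with the originally planned GEE reported alongside.

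No new data or visits are needed. P values become slightly larger and intervals slightly wider: for a single contrast, (2.032/1.960) × (1/0.972) = 1.067, about 7%, where 2.032 is the t critical value on 34 df. The remaining cost is a documented departure from the published method.

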## Discussion

### Anticipated Findings

This study is designed to evaluate whether honey-based dressings can enhance wound healing in patients with deep neck abscesses compared to standard dressings. The anticipated findings are that honey dressings, due to their antibacterial, anti-inflammatory, and immunomodulatory properties, will result in faster and more effective healing outcomes. These outcomes will be assessed clinically, bacteriologically, systemically, and through biomarker analysis of IL-1, TNF-α, and VEGF expression.

Honey has long been used in traditional medicine, and modern research has supported its effectiveness in wound care. Previous studies have demonstrated honey’s ability to promote healing in burns, surgical wounds, and chronic ulcers. Its unique properties—such as high osmolarity, low pH, hydrogen peroxide production, and rich content of antioxidants and bioactive compounds—contribute to its antimicrobial and healing potential [17,18,37]. Particularly, Manuka honey has shown strong efficacy against drug-resistant bacteria, including methicillin-resistant *Staphylococcus aureus* and vancomycin-resistant *Enterococcus*, and has been successfully used in chronic wound treatment [17,38]. In vitro studies have also indicated that honey stimulates the release of inflammatory cytokines such as IL-1, TNF-α, and IL-6, which play essential roles in wound healing [37]. Despite these promising results, there remains a lack of clinical studies specifically examining the use of honey for deep neck infections, which are serious, rapidly progressing conditions with potential airway and systemic complications [2,3,6].

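### Six outcomes are tested at an unadjusted P<.05 and none is named primary, so the chance of at least one false-positive result is about 21% to 34%, not 5%

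*Protocol article*

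**What the plan says.** The abstract lists the outcomes side by side: "Proinflammatory cytokines and growth factors, wound size, Bates-Jensen Wound Assessment Tools scoring, and quantitative bacterial colony identification will be all evaluated and assessed". The Outcomes section specifies the tissue markers, "including quantification of IL-1, TNF-α, and VEGF expression", which makes six outcomes in all.

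Under Statistical Analyses, groups are compared "at each time point (days 1, 7, and 14), either an independent" *t* test or a Mann-Whitney U test. For the treatment effect over time and its interaction with group, "a generalized estimating equation analysis will be performed". A *P* "value of <.05 will be considered statistically significant". The section gives no adjustment, no ranking of outcomes and no sidedness.

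The visits differ by outcome. The Measurements section says: "On day 7, wound size measurements and BWAT scoring were repeated". The Outcomes section assigns "the first and fourteenth days for bacterial colony identification from wound bed swabs and cytokine and growth factor expression analysis from tissue samples".

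The Sample Size section uses one quantity only, wound closure in cm, with Zα=1.64, 90% power and 18 per group. The article does not call that quantity primary, and it does not say at which visit or by which test it will be judged.

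**The concern.** A trial that asks whether a dressing is effective needs one result that decides the answer. Here the error rate used to size the trial belongs to one comparison, while the analysis applies the same threshold to several. The plan does not say which of them counts, so a single small *P* value among six outcomes could be reported as evidence for honey without departing from anything written.

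The biomarkers add a further looseness. The Discussion presents honey as anti-inflammatory and also reports laboratory work in which "honey stimulates the release of inflammatory cytokines such as IL-1, TNF-α, and IL-6, which play essential roles in wound healing". No expected direction is stated for IL-1 or TNF-α, so a difference either way could be read favourably after the fact.

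**Working it through.** **1. The plan's own figure.** Inputs from Sample Size: control mean 0.266 cm, SD 1.183 cm, honey mean 1.433 cm, so the difference is 1.433 − 0.266 = 1.167 cm.

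n per group = 2 × [1.183 × (1.64 + 1.28) / 1.167]² = 17.5, rounded up to 18. The stated size is reproduced, with one outcome, one comparison and a one-sided α of .05. With two-sided .05 the same formula gives 21.6, so 22.

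**2. Counting the tests.** Day 1 is baseline and is left out.
- Day 14: wound size, BWAT, colony count, IL-1, TNF-α, VEGF = 6 tests.
- Day 7: wound size and BWAT only = 2 tests.
- Scheduled post-baseline comparisons: 6 + 2 = 8.

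**3. Chance of at least one *P*<.05 with no true effect, independent tests.**
- Either direction, 6 tests: 1 − 0.95⁶ = 26.5%.
- Either direction, 8 tests: 1 − 0.95⁸ = 33.7%.
- Favouring honey, two-sided tests (.025 in each tail), 6 tests: 1 − 0.975⁶ = 14.1%.
- Favouring honey, 8 tests: 1 − 0.975⁸ = 18.3%.

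**4. Allowing for correlation.** The article gives no correlations, so they are assumed. *t* tests were simulated with 18 per group and 20,000 runs per setting. Two visits of the same outcome were correlated 0.5 in the second row below and 0.6 in the third.

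| Correlation between outcomes | Either direction, 6 tests | Either direction, 8 tests | Favouring honey, 6 tests | Favouring honey, 8 tests |
|---|---|---|---|---|
| 0 (formula) | 26.5% | 33.7% | 14.1% | 18.3% |
| 0.3 | 24% | 30% | 12% | 15% |
| 0.5 | 21% | 26–27% | 11% | 13% |

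At a correlation of 0.7 the either-direction figures fall further, to about 16% and 21%.

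**5. Power if the primary test is two-sided.** The noncentrality is 1.167 / (1.183 × √(2/18)) = 2.96 on 34 degrees of freedom. Two-sided power at .05 is 82% from the noncentral *t* distribution (84% by the normal approximation). One-sided power is about 90%.

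**The case against.** **The article is condensed.** Multiplicity handling is often left to an analysis plan, and neither that plan nor the registry record is at hand. A primary outcome may be named there. Wound closure, as the basis of the sample size, is also an implied lead outcome. This has weight, but the article has its own Outcomes and Statistical Analyses sections, and they state a threshold and apply it without distinction. Which outcome decides the question is core protocol content. An implied lead outcome with no visit and no test does not settle it.

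**The outcomes are correlated.** BWAT itself scores size and depth, so it overlaps with wound size, and the independence figures are the upper end of the eight-test range. This stands, and it is why a range is given.

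**Stronger readings that the document does not support:**
- *A false claim for honey has a 1 in 4 to 1 in 3 chance.* Those figures count errors in both directions. They would apply to honey alone only if every test were one-sided at .05 and independent. The sample size is one-sided, but Statistical Analyses does not state sidedness. Even if either direction on IL-1 and TNF-α counted as support, independent two-sided tests would give 1 − 0.975⁴ × 0.95² = 18% for six and 1 − 0.975⁶ × 0.95² = 22% for eight. The cytokine sentence is Discussion background on in vitro work, not a decision rule.
- *Every outcome is tested at every visit.* General sentences mention days 1, 7 and 14, but Table 1 and the detailed text put only wound size and BWAT on day 7.
- *The GEE tests can be added as if independent*, for example 1 − 0.95¹⁴ = 51% for 14 tests. They reuse the same data, so they add something, but not that much.

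Nor does the article say that one positive result suffices for a claim. The point is that nothing in it prevents this.

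**Conclusion.** The concern holds in this form: six outcomes share one unadjusted threshold and none is designated as deciding effectiveness. For between-outcome correlations from 0.5 to 0, the chance of at least one false-positive result in either direction is about 21% to 27% for the day-14 tests and 26% to 34% for all eight scheduled post-baseline tests. For two-sided tests, false positives favouring honey are roughly half as likely, about 11% to 18%. Even the low end is more than four times the 2.5% of a single two-sided test.

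The sizes rest on assumed correlations, *t* tests at 18 per group and the schedule as detailed in Measurements and Outcomes. GEE tests would raise them somewhat, as would separate analysis of length, width and depth. Stronger correlation would lower them.

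**What to change.** Name wound-size reduction from day 1, the quantity that sized the trial, as the single primary outcome. Define how it is calculated, and fix one visit, one test and its sidedness before allocation is opened. Base the effectiveness conclusion on that result alone.

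The Blinding section discloses allocation only after database lock, but the Results section says analysis is underway. If allocation is already open, report the choice as made afterwards. In either case, check it against the registry entry.

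Apply Holm to BWAT and colony count, or report them with confidence intervals and no significance claim. Label IL-1, TNF-α and VEGF exploratory, with the expected direction stated for each.

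No new data are needed. The costs are that secondary results lose stand-alone claims and that, with a two-sided primary test at .05, the power under the stated inputs must be restated as about 82% rather than 90%.
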